## Background

Chemotherapy is a major type of cancer treatment using chemical medications to affect cancer cell growth, division and reproduction. Regardless of the route of administration, chemotherapy drugs are introduced into the blood stream, so that chemotherapy can cause various degree of damage to other normal organs and tissues while killing cancer cells, further causing a series of serious adverse effects/toxicity.

Hair loss is an obvious side effect of chemotherapy. The incidence of chemotherapy-induced hair loss is as high as 65% in patients receiving chemotherapy and in some is even up to 80–100% in patients receiving specific agents, such as doxorubicin and docetaxel [1–3]. Although hair loss itself does not cause damage to the body and threaten life, it can induce persistent negative emotions such as anxiety, depression and negative evaluation of self-image, which in turn reduces quality of life [4]. The hair loss caused by chemotherapy is usually reversible; however, in most cases, the color of the new hair is grayish or different from the previous color, and the hair texture also shows some changes, such as being rougher, slower growing and sparser [5, 6]. Besides, contemporary social media and excessive attention to appearance have put more pressure on patients, with 8% of patients saying that they refuse chemotherapy because of fear of alopecia [7]. Even some female patients said that having no hair is more difficult to tolerate than mastectomy [8].

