### Subjects

A total of 214 eligible patients will be recruited at different clinical centers. Inclusion criteria include: (1) women with stage-I or -II breast cancer aged between 18 and 75 years; (2) receiving first chemotherapy; (3) planning to receive chemotherapeutic agents containing taxanes or/and anthracyclines; (4) the chemotherapy regimen will last for at least six cycles with every 3 weeks a cycle; (5) adverse events assessed using WHO toxicity classification criteria < grade II; and (6) a life expectancy of at least 6 months. Exclusion criteria are: (1) patients with a medical history of hair transplantation; (2) patients suffering from psoriasis or severe scalp infection; (3) hair loss induced by alopecia areata, alopecia totalis or scalp injury, etc.; (4) pregnancy, lactation or potential pregnancy; (5) allergy to some specific foods, like black soybean; (6) severe cardiac, hepatic, renal, pulmonary and hematic lesions or other diseases which will affect their survival; (7) those who have any severe mental or behavioral disorders who cannot be fully informed; (8) suspected of or with a history of alcohol and/or drug abuse; (9) cannot understand or fill in questionnaires because of cognitive disorders or a low level of literacy; and (10) a variety of factors affecting drug taking and absorption, such as the inability to swallow, chronic diarrhea, intestinal obstruction, etc. Eligible patients will be invited to participate in this study after obtaining their written consent form. All participants will be closely monitored in the study.

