### Randomization and blinding

Each subject will obtain an unique number after completing written consent. A computer-blocked random number sequence with a block size of four will be generated centrally by a statistician not involving in this study. As YH0618 granule and placebo show the same appearance, a double-blind model will be adopted. Therefore, the randomization sequence and different groups will be kept hidden from subjects, practitioners, data collectors and statisticians.

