### Statistical analysis

All analyses will be performed based on intention-to-treat principles, any missing data in the follow-up visits will be imputed using multiple imputation. Descriptive analyses as means and standard deviations (SDs) will be used to describe the demographics and clinical characteristics of the participants. The primary efficacy analysis compared the hair-loss grading between YH0618 granule and control before the fifth chemotherapy using Fisher’s exact test. The changes of hair diameter between the two groups after four cycles of chemotherapy will be compared by an independent samples *t* test. A multivariable logistic regression model will be used to explore the treatment effect. Potential confounding variables will be identified as those that differ among treatment groups at baseline and are significantly associated with outcomes. Changes from baseline to the final assessment in quality of life assessed by the FACT-B and objective indicators in the blood will be compared using Wilcoxon rank sum tests. Unless otherwise specified, two-sided statistical tests will be used and the significance level will be set at *p* < 0.05.

In this trial, an interim analysis will be performed when approximately two thirds of the planned observations are enrolled. The results are analyzed by the statistician and only DSMB members have access to the results to test for futility, safety and efficacy of the trial. A predefined stopping rule will be applied to the data to determine whether it is futile to continue enrollment.

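### The covariate rule for the exploratory logistic model picks factors by chance baseline difference and outcome significance; it should be replaced by a fixed set of baseline covariates

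*Protocol article*

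**What the plan says.** All on this point comes from the protocol article.

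- **Statistical analysis, primary comparison.** "The primary efficacy analysis compared the hair-loss grading between YH0618 granule and control before the fifth chemotherapy using" Fisher's exact test. No covariate enters it.
- **Statistical analysis, adjusted model.** "A multivariable logistic regression model will be used to explore the treatment effect". No covariate is named. Instead: "Potential confounding variables will be identified as those that differ among treatment groups at baseline and are significantly associated with outcomes".
- **Statistical analysis, test level.** Unless stated otherwise, "two-sided statistical tests will be used and the significance level will be set at" p < 0.05.
- **Subjects.** Patients are eligible when "planning to receive chemotherapeutic agents containing taxanes or/and anthracyclines", so taxane, anthracycline and combined regimens are all admitted. Study design names three recruiting hospitals.
- **Randomization and blinding.** "A computer-blocked random number sequence with a block size of four will be generated centrally". The article describes no stratification factor.
- **Background.** "The incidence of chemotherapy-induced hair loss is as high as 65% in patients receiving chemotherapy", rising to 80–100% with certain agents, for which doxorubicin and docetaxel are the examples.

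**The concern.** Both conditions of the rule look at trial data, and neither measures what a covariate is worth in the model.

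The first asks whether the arms differ at baseline. With 1:1 randomisation any such difference is chance, so a test at p < 0.05 flags a powerful predictor and a useless one equally often, about once in 20 trials. A strong predictor that happens to be well balanced, or moderately imbalanced but short of the threshold, is left out.

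The second asks for a significant association with the outcome. The model is then known only once the outcomes are known, and two data sets from the same design could be adjusted for different variables.

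At stake are the precision of the adjusted estimate and its standing as a planned analysis. The logistic model is the only place in the stated analysis of hair loss where a prognostic factor can be taken into account.

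**Working it through.** **Inputs from the article (Estimation of sample size; Study design).** Hair loss below grade II in 50% with YH0618; difference from control 15 points, so control 35%; two-sided alpha 0.05; power 80%; 85 evaluable and 107 randomised per group; ratio 1:1.

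**The plan's own figure.** The attrition step reproduces: 85/(1 − 0.20) = 106.25, rounded up to 107. The 85 does not. With p̄ = (0.50 + 0.35)/2 = 0.425,

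n = [1.96·√(2 × 0.425 × 0.575) + 0.8416·√(0.50 × 0.50 + 0.35 × 0.65)]² / 0.15² = (1.370 + 0.582)² / 0.0225 ≈ 170 per group.

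For 50% versus 35%, analytic power is 51% at 85 per group and 60.4% at 107. This is a separate matter from the covariate rule; it matters here only because it sets the power level from which the comparison below starts.

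**Assumptions, because the article gives no figure.** One binary regimen factor, held by 30% or 50% of patients; odds ratio of regimen for the outcome 2, 4 or 8; outcome dichotomised at grade II; marginal rates held at 35% and 50%; simple 1:1 allocation; differing and associated both read as chi-square p < 0.05. The unadjusted analysis is a chi-square test. A Mantel-Haenszel test stratified by regimen stands in for the adjusted logistic model. There were 40,000 simulated trials per scenario, giving a Monte Carlo standard error of about √(0.6 × 0.4/40,000) = 0.24 points.

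**Step 1: how often the rule selects regimen.** The baseline condition alone is met in 4.5% to 5.6% of trials, whatever the odds ratio. Both conditions together are met in 2.4% to 5.5%. Regimen is therefore left out in about 94% to 98% of trials.

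**Step 2: type I error under the rule.** 4.3% to 5.2% over all null scenarios. It is not inflated.

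**Step 3: power at 107 per arm.**

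| Regimen share | Regimen OR | Selected by rule | Power, rule | Power, fixed adjustment | Gain (points) |
|---|---|---|---|---|---|
| 50% | 2 | 3.1% | 59.2% | 61.2% | 2.0 |
| 50% | 4 | 4.5% | 59.7% | 64.8% | 5.1 |
| 50% | 8 | 4.7% | 60.2% | 71.0% | 10.8 |
| 30% | 2 | 2.9% | 59.5% | 61.2% | 1.7 |
| 30% | 4 | 4.9% | 59.8% | 64.1% | 4.3 |
| 30% | 8 | 5.1% | 59.7% | 67.0% | 7.3 |

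The rule performs like no adjustment (59.1% to 59.6% unadjusted). At odds ratio 2 part of the gap is discreteness of the unadjusted test: against the analytic 60.4% the gain is 61.2 − 60.4 = 0.8 points. The range is therefore about 1 to 11 points. At 85 per arm the gains are about 0 (odds ratio 2), 2 to 3 (odds ratio 4) and 5 to 8 (odds ratio 8).

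**Step 4: imbalance that slips under the threshold.** At 107 per arm and a 50% share, the baseline test needs a difference of about 1.96·√(2 × 0.25/107) = 13.4 points. Without stratification a difference of 10 points or more occurs in 12% to 15% of trials at 107 per arm, and in 15% to 20% at 85. Many of these fall below the threshold and would go unadjusted.

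**The case against.** The strongest reply is about scope. The rule governs a model that the article presents as exploratory. The primary Fisher test is valid under randomisation with or without covariates, and Step 2 shows no excess of false positives. All of this stands: the point concerns efficiency and pre-specification, not a bias in the main result.

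A reader might infer that regimen is a major determinant of hair loss within this trial, since Background sets 65% against 80–100%. The article does not support that. Its two examples of high-risk agents are one anthracycline and one taxane, the Discussion lists drugs of both classes together, and eligibility is already confined to those classes. The contrast is between chemotherapy in general and agents such as those used here, not between the admitted regimens. The regimen effect could be small, and the gain would then be near zero. An extreme split, such as 10% against 60% below grade II, is an odds ratio of (0.6/0.4)/(0.1/0.9) = 13.5; no figure in the article justifies it.

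A reader might also infer that the randomisation fails to balance regimen. It balances regimen on average; only chance imbalance remains. The article describes no strata, but it condenses a fuller protocol, so its silence is no evidence that there are none.

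Finally, only the outcome condition uses the word for statistical significance; the baseline condition names no test. Reading it as p < 0.05 is natural given the general test level, but it is an inference. An undefined difference would leave more discretion, not less.

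**Conclusion.** The point holds as a moderate one. The article fixes a selection rule that is poorly suited to a randomised trial: it disregards prognostic strength and makes the adjusted estimate depend on the data. On the p < 0.05 reading, a factor such as planned regimen would be used in about 2% to 6% of trials. The price is precision, about 1 to 11 points of power at 107 per arm, together with chance imbalance that goes uncorrected. Those sizes rest on assumed regimen shares of 30% or 50% and odds ratios of 2 to 8, not on figures in the article. The criticism of the rule itself does not depend on them. Neither the validity of the primary test nor its type I error is in question.

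**What to change.** Delete the selection sentence. In its place name, before any unblinded data are seen (including those for the planned interim analysis), a fixed set of baseline covariates for the logistic model: chemotherapy class planned at randomisation (anthracycline, taxane or both), centre, and age. Include them whatever the baseline table shows. Use the planned class rather than the agents actually given, because treatment received can change after allocation and is then not a baseline variable. If the randomisation list is stratified by any of these factors, include those factors in the model.

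The cost is a change of wording, with no new data if planned regimen is recorded at entry. The model spends a few degrees of freedom, and sparse regimen or centre categories may need pooling; the pooling rule should be written down at the same time.

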## Discussion

Chemotherapy-induced hair loss occurs usually due to the high mitotic rate of hair follicles instead of a non-androgenic mechanism, and can manifest as alopecia totalis, telogen effluvium, or, less often, as alopecia areata [27]. Severe hair loss occurs most often with drugs such as doxorubicin, daunorubicin, docetaxel, paclitaxel, cyclophosphamide and etoposide, which are common chemotherapy agents used for breast cancer patients. Even some standard chemotherapy regimens can induce permanent thinning or hair loss. Although scalp-cooling is a method approved by the FDA for preventing both permanent and temporary hair loss, concerns about this method have been raised [6, 28]. Therefore, this is the first strict randomized, double-blind, multi-center controlled trial to evaluate the effect of a medicinal and edible compound prescription on chemotherapy-induced hair loss. The proposed study may provide direct and convincing evidence to support YH0618 as an adjuvant treatment for reducing chemotherapy-induced toxicity, which could be introduced into clinical settings. Our achievements will provide a safe and effective way for reducing chemotherapy-induced hair loss and improving patients’ quality of life.

## Trial status

The protocol version 1. Recruitment will start in June 2019 and the trial is expected to be completed in December 2020.

## Data Availability

Not applicable

## Abbreviations

ALT: Alanine aminotransferase
AST: Aspartate transaminase
BUN: Blood urea nitrogen
CE: Conformité Européenne
DSMB: Data and Safety Monitoring Board
FACT-B: Functional Assessment of Cancer Therapy-Breast Cancer
FCC: Federal Communications Commission
FDA: Food and Drug Administration
IgM: Immunoglobulin M
RHoS: Restriction of Hazardous Substances
UA: Uric acid
WHO: World Health Organization
